**Figure 1 figure1:**
[figure not shown]
Overall design of the PARACT (PARAmedical Interventions on Patient ACTivation) multicentric study.

First, a robust preimplementation analysis will be performed by using the Theoretical Domains Framework (TDF) linked to the COM-B (Capability, Opportunity, Motivation, and Behavior) model to identify the obstacles and facilitators to implementing new nursing practices in each context. Then, using the Behavior Change Wheel, a strategy for implementing the PAM-13 will be personalized, depending on the specificities of each context, in order to encourage acceptability by the nursing staff involved in the project. This preimplementation analysis will be carried out via a qualitative study through semistructured interviews.Once this step is complete, the second step of enrolling patients in the study can begin. The patient will be included in the study for a period of 12 months. During his or her involvement, the patient care pathway will be studied, particularly to collect all relevant contacts of oncology nurses and other health professionals involved in the cancer care pathway. The axes of nursing care will also be collected. The primary goal is PAM-13. Secondary factors to be measured are the patient’s level of anxiety according to the Hospital Anxiety and Depression (HAD) scale, the assessment of patients’ quality of life as measured by the European Quality of Life-5 Dimensions-3 Level (EQ-5D-3L) questionnaire, and the level of health literacy using the REALM-R. The oncology nurses in charge of treating the patient in the cancer care pathway will be responsible for completing each of the questionnaires when the patient is at the hospital for his/her intravenous chemotherapy or immunotherapy treatment. The questionnaires will be completed 3 times in the course of 1 year: (1) at the time of the patient’s enrollment in the study, (2) at 6 months, and (3) at 12 months.Finally, at the end of the study period and patient follow-up, a postimplementation analysis will be performed through semistructured interviews, using the TDF to probe implementation problems at each site. Four implementation elements will be measured within the framework of RE-AIM: reach the population (R), effectiveness of the intervention (E), adoption and adaptation of the intervention to its context (A), and maintenance of the intervention (M) [66].

### Research Design

#### Step 1: Preimplementation Analysis

Qualitative data will be collected in the form of individual semistructured interviews, with oncology nurses involved in setting up and conducting PAMs in different comprehensive cancer centers. This qualitative phase will take place before implementation. According to Malterud, qualitative research offers strong potential to understand a problem in all its dimensions from all angles and to study a phenomenon not yet documented. In addition, the production of qualitative data is essential to be able to question the caregivers’ representations [67]. It will enable us to assess the evolution of the perceptions of the nurses’ teams concerned in this study, the activation of the patients, the perception of their own roles, and their perceived and actual implications in this project. Ten semistructured interviews will be scheduled at each center. The special feature of TDF is that it specifically questions individual motivation and capacity factors, in addition to taking into account the physical and social environment of the context concerned by the implementation [68]. We will perform a qualitative analysis based on TDF to (1) build the semistructured interview grid [68,69], (2) conduct a qualitative analysis [70], (3) diagnose obstacles and facilitators to implementation [68], (4) draw up the intervention to ensure better acceptability, linking the TDF to the COM-B model and then to the Behavior Change Wheel [69].

Qualitative data will be analyzed in order to generate themes, that, in poststudy findings, can be associated with the TDF [68,69,71-74]. Specifically, we will apply the methodology framework proposed by Braun and Clarke [75].

Familiarization with the data: This phase involves reading and rereading the data to become immersed and intimately familiar with its content.Generating initial codes: This phase involves generating succinct codes that identify important features of the data that might be relevant to answering our research question. It involves coding the entire data set, and after that, collating all the codes and all relevant data extracts together for later stages of analysis. Nvivo 11 pro software (QSR International) will be used to perform the analyses.Searching for themes: The collection of codes will be worked on in pairs with a PhD researcher in sociology to validate a comprehensive interpretation and a grouping of code elements into themes.The resulting themes will be compared to the TDF domains, independently by 2 researchers, and then compared and discussed. Items that could not be included in the TDF framework will be thematized separately.Finally, a more refined coding will be used for each part of the verbatim used to illustrate the themes.

The COREQ (consolidated criteria for reporting qualitative research) will guide the reporting of the qualitative analysis [76].

#### Step 2: Implementation of the PAM-13 and Patient Enrollment

##### Number of Subjects Needed

As this is an implementation study, it is not possible to calculate a sample size required to respond to an efficacy hypothesis. The goal is to observe how many patients will be involved in the measurement of PAM-13 in real life. It is therefore not possible at this juncture to determine a set number of patients to be reached before ending the study.

Nevertheless, in order to stay within the confines of the study budget, it seems reasonable to limit the number of enrollments to approximately 150 patients per center in order to have a sufficient understanding of the implementation of the PAM-13 in the different facilities. A total of up to 600 patients will be included in the 5-site study (up to 150 patients per site). Two establishments will include a maximum of 75 patients per site.

We will implement the PAM-13 at each center and the study may begin enrolling patients, as outlined below.

##### Screening and Inclusion

The oncologists, and, as a priority, the cancer nurse navigator (if the establishment employs one) or an oncology care nurse involved in the announcement of the diagnosis, and finally, a registered nurse at the choice of the investigator of the different investigative centers will suggest patients who meet the inclusion criteria to participate in the PARACT study. First, the procedure and aim of the study will be explained to the patient, and then, he or she will be given a consent form to sign. Patients will have a period of reflection of at least half an hour—seemingly sufficient—considering the extremely low risk factor of participating in the PARACT study. The patients’ inclusion must be completed within 15 days of the consultation to announce the cancer pathology. The patient will be included in the study for a period of 12 months. During his or her involvement, the patient care pathway will be studied, particularly to collect all relevant contacts of oncology nurses and other health professionals involved in the cancer care pathway. Axes of nursing care will also be collected. The primary goal is PAM-13. Secondary factors to be measured are the patient’s level of anxiety according to the HAD scale, the assessment of patients’ quality of life as measured by the EQ-5D-3L questionnaire, and the level of health literacy by using the REALM-R screening instrument. The oncology nurses in charge of treating the patient in the cancer care pathway will be responsible for completing each of the questionnaires when the patient is at the hospital for his/her intravenous chemotherapy or immunotherapy treatment. The questionnaires will be completed 3 times in the course of 1 year: (1) at the time of the patient’s enrollment in the study, (2) at 6 months, and (3) at 12 months.

##### Patient Inclusion Criteria

The inclusion criteria for this study are as follows. The patient must be at least 18 years of age upon enrollment. The patient with cancer must have an estimated life expectancy of at least one year. The patient must be undergoing treatment involving intravenous chemotherapy or immunotherapy for any cancer or both of them as outlined in the decision of the multidisciplinary concertation meeting. The patient must be affiliated with a health insurance policy or entitled to social security coverage.

##### Patient Exclusion Criteria

Patients are excluded from this study for any of the following reasons. The patient has declined to participate. The adult patient is protected under legal guardianship or curatorship. The patient is unable to understand the procedure of the study. The patient has presented prior documentation indicating cognitive or psychiatric disorders. The patient does not understand the French language.

##### Validity and Reliability of the Questionnaires

The PAM-13 was developed by Hibbard et al to assess knowledge, skills, and confidence in managing health [30,31,77]. It is used in several contexts of disease and in many countries around the world [31,33-39]. Specifically, Prey et al have demonstrated its reliability and validity with inpatient individuals in oncology [40]. The validated French version will be used. The HAD scale will be used to measure the evolution of patients’ anxiety [78]. The United Kingdom National Health Service and French National Authority for Health recommend its use to assess anxiety and depression among inpatient individuals. Its reliability and validity are widely recognized [78-80]. The EQ-5D-3L is a validated tool for measuring the quality of life [81]. Several studies have been published and have provided evidence to support the validity and reliability of the EQ-5D in studies of cancer [82]. This self-questionnaire explores 5 dimensions: mobility, self-care, usual activities, pain/discomfort, and worry/pressure. The REALM-R test validated in French will be used to measure the level of patients’ health literacy. Bass et al provided evidence to support the validity and reliability of the shortened version of the REALM, which is named as REALM-R [26]. Grandjacquot recently adapted it in the French language, and it proved effective in detecting inadequate levels of health literacy [27].

#### Step 3: Evaluation of the Implementation

First, at the end of the inclusion period and patient follow-up, a postimplementation analysis through semistructured interviews using the TDF to investigate implementation obstacles and facilitators at each site will be performed. The same sample and qualitative analysis methodology as that relating to the preimplementation analysis will be used.

Second, 4 implementation outcomes will be measured. These outcomes would have been collected over the entire study by using the RE-AIM [66]. See overview of the implementation outcomes from the RE-AIM (Multimedia Appendix 1).

### Statistical Analysis

#### Design

The analyses will be performed using R 3.2.5 (R Foundation [83]) software. The characteristics of the patients will be described using the following statistics: for quantitative variables, number of available data, means, standard deviation, median, quartile 1, and quartile 3; and for qualitative variables, absolute and relative frequencies (expressed as percentage). To calculate patient activation, the guidelines provided by Insignia Health will be followed [84]. Activation will be measured quantitatively at enrollment, at 6 months, and at 12 months. The difference will be calculated between the baseline measurement and the 12-month measurement for all patients at each center. The mean of this difference will be compared between the comprehensive cancer center that employs a nurse navigator and each of the 4 other facilities. Activation will also be compared according to its evolution during the 12 months of follow-up by using a mixed linear model. The variables influencing the difference in the activation score will be included in this model. The search for factors influencing the activation level will be carried out using the following methods:

Initially, univariate analysis with chi-squared tests (or Fisher exact if the conditions are not met) for qualitative variables and Student two-sided *t* test (or Wilcoxon test if the conditions are not met) for quantitative variables will be performed.Subsequently, multivariate analysis with all exploratory variables with a significance threshold lower than 0.2 will be introduced into the multivariate model. The interactions between the variables will be ensured in advance. If an interaction is detected, the choice of the variable to be introduced will be made based on clinical relevance. The choice of the best multivariate model will be made using a selective downward procedure on the Akaike information criteria.Health literacy will be assessed via the score obtained by the REALM-R (a score <6 demonstrating a low health literacy score). The before/after health literacy increase will be assessed using a McNemar chi-square test using the score qualitatively (threshold at 6). A logistic regression model with random effect will be used in the multivariate analysis to eliminate any confounding factors with the same methodology as described above. The same methodology will be applied to the HAD scale (threshold at 11). The analysis of quantitative scales such as the EQ-5D-3L or the confidence level will be performed with matched (or otherwise Wilcoxon) Student tests between inclusion and M12. Random multivariate linear models will be implemented to adjust for any confounding variables. For the EQ-5D-3L, analyses of time until deterioration can be implemented if necessary.

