#### Degree of Statistical Significance

The results will be considered significant at the 5% threshold.

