## Discussion

The purpose of this project is to implement the PAM-13 within oncology nursing practices at 5 comprehensive cancer centers. To our knowledge, no measurement of patient activation has been used in routine practice or has been experimented in cancerology in France. Analyzing the impact of nursing intervention through such a measure, depending on the type of facility, could lead to strengthening some of them, modifying care practices, and enabling better patient management. In the end, this evaluation via the PAM-13 should allow for a greater understanding of the contribution of these specific nursing interventions of care, the objective being to confirm better activation of the patient in establishments that use a combined set of measures.

The use of an activation measure would constitute a major change in the management of patients with cancer. As the patient’s activation is evolutive, the implementation of targeted nursing interventions would increase the activation. A number of programs have demonstrated their ability to increase the level of patient activation [85-87]. They generally focus on the acquisition of new skills by patients and support a sense of ownership of their health. These different research studies showed that peer support, changes in the patient’s social environment, coaching, and health education courses have been deemed valuable [85-87]. Furthermore, measuring the level of activation and the implementation of measures intended to increase the level of activation would constitute a significant advantage in reducing social health inequalities [88]. Indeed, different studies having implemented this type of intervention have shown that the patients who experience the lowest activation levels are those who tend to show the greatest increase in the activation level [46]. This may be partially due to a “ceiling” effect; not much improvement can be made in patients who already demonstrate high levels of activation. However, this also shows that effective interventions can help disengaged patients become proactive toward their health [85,89,90].

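### One navigator center against four others: the comparison can show that centers differ, but it cannot attribute a difference to the navigator or confirm better activation by type of establishment

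*Protocol article*

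**What the plan says.** All references are to the Protocol article.

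- **Statistical Analysis, Design.** The baseline-to-12-month difference in activation is calculated for patients at each center. Its mean is then "compared between the comprehensive cancer center that employs a nurse navigator and each of the 4 other facilities". A mixed linear model for the course of activation, with influencing variables added, is also planned. No center or navigator term is named for it.
- **Degree of Statistical Significance.** "The results will be considered significant at the 5% threshold".
- **Implementation Study (text below Figure 1).** For each site, "a strategy for implementing the PAM-13 will be personalized, depending on the specificities of each context".
- **Objective of This Study.** Centers are described as differing in nursing specialties and supportive care, and activation is supposed to depend largely on these.
- **Number of Subjects Needed.** The article states that "it is not possible to calculate a sample size required to respond to an efficacy hypothesis". It sets caps instead: "A total of up to 600 patients will be included in the 5-site study (up to 150 patients per site"), and "Two establishments will include a maximum of 75 patients per site".
- **Discussion.** The evaluation is meant to clarify what specific nursing interventions contribute, "the objective being to confirm better activation of the patient in establishments that use a combined set of measures".
- **Formal objectives (Abstract and Objective of This Study).** There are three: evaluate implementation of PAM-13, identify obstacles and facilitators, and produce dissemination recommendations.

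**The concern.** With one center on one side of the contrast, there is no replication of navigator status. Whatever makes that center different in 12-month change is counted in the same number as the navigator. The article itself names two such sources, the nursing and supportive-care offer and the tailored implementation strategy. The Screening and Inclusion section adds a third: where a navigator exists, that nurse has priority in approaching patients, so recruitment may itself differ with navigator status.

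A 5% threshold then invites a yes/no answer, and the Discussion speaks of confirming better activation by type of establishment. What is at stake is the interpretation: ordinary variation between hospitals could be reported as an effect of how a hospital organizes its nursing.

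**Working it through.** **1. Reproduce the plan's figure.** Three centers at 150 and two at 75: 3 × 150 + 2 × 75 = 600, which agrees with the stated maximum. The article gives no power, effect size or SD, so nothing further can be reproduced.

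**2. Can any planned analysis separate navigator from center?** Write the mean change at center *j* as μ + β·(navigator at *j*) + *c_j*, where *c_j* is everything else about that center. The navigator center minus center *j* estimates β + *c*₁ − *c_j*. The term *c*₁ is in all four contrasts, and no second navigator center exists from which to estimate it apart from β.
- Using each patient as their own control removes stable patient differences, but not center differences in *change*.
- Patient-level covariates remove measured case mix, but not staffing, supportive care or the tailored strategy.
- A mixed model can include center or navigator, but it cannot identify both freely.

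**3. How often would one test be significant with β = 0?** Assumptions (not in the article): within-center patient SD of change 15 points; between-center SD τ of 1, 2 or 3 points; enrollment at the caps; two-sided 5% test on patients. The article names no test for this contrast, and states two-sidedness only for the univariate factor search.

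se = 15·√(1/n₁ + 1/n₂); rejection probability = 2·[1 − Φ(1.96·se / √(se² + 2τ²))]

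| Center sizes | se | τ = 1 | τ = 2 | τ = 3 |
|---|---|---|---|---|
| 150 v 150 | 1.73 | 13% | 31% | 46% |
| 150 v 75 | 2.12 | 10% | 24% | 38% |
| 75 v 75 | 2.45 | 9% | 20% | 33% |

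Example, 150 v 150 and τ = 2: √(3 + 8) = 3.317; 1.96 × 1.732 / 3.317 = 1.02; two-sided probability 0.31.

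These values of τ are small. As a share of total variance, τ² / (τ² + 225), they are 0.4%, 1.7% and 3.8%.

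**4. Sensitivity.** A separate simulation with an assumed between-center variance share (ICC) of 0.01 to 0.05 gives single-test rejection of 14% to 51% at full enrollment, and 10% to 41% if only 60% of those patients are analyzed.

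**5. Multiplicity (secondary).** Four tests that share one comparator, each at 5%, with no center variation at all:

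| Navigator center | Other centers | At least one false positive | Dunnett critical value | Width relative to 1.96 |
|---|---|---|---|---|
| 150 | 150, 150, 75, 75 | 16.4% | 2.46 | 1.25 |
| 75 | 150, 150, 150, 75 | 14.1% | 2.41 | 1.23 |

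For independent tests it would be 1 − 0.95⁴ = 18.5%.

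**6. Does splitting alpha cure step 2?** No. With Bonferroni at 0.05/4 = 0.0125 and ICC 0.01 to 0.05, at least one of the four tests still rejects in 21% to 77% of cases at full enrollment. The aliasing dominates.

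**The case against.** The strongest reply is that this is an implementation study in the realistic-evaluation tradition. Differences between centers and their tailored strategies are what it sets out to study, and no sentence says that a difference will be credited to the navigator. Much of this stands, and it limits the point in five ways.

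- **The formal objectives are not at risk.** A reader might infer that the trial fails its aim. None of the three objectives is a navigator effect. The word *confirm* occurs only in the Discussion, and there it concerns establishments with a combined set of measures, not a navigator as such. The article does not say which centers those are.
- **There is no flat contradiction over sample size.** A reader might take the sample-size section as ruling out any efficacy question. It says only that a sample size for one cannot be calculated.
- **The dissemination recommendations are not shown to depend on this test.** The Discussion bases them on a detailed description of how PAM-13 was used, and their subject is deploying the measure. No text feeds the navigator contrast into them.
- **Multiplicity may be handled elsewhere.** The full protocol and analysis plan are not shown, so a missing alpha split is not in itself a fault of this article.
- **The rejection rates rest on assumed SDs.** They also reflect real center differences, and become errors only if the difference is attributed to the navigator.

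One part of the reply does not stand. The planned mixed model and covariate selection are a genuine plan for adjustment, but they do not address aliasing, and an analysis plan cannot supply a second navigator center. The article also sets a significance threshold and a confirmatory purpose, which goes beyond describing centers.

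**Conclusion.** The point holds in a limited form. The navigator contrast is completely aliased with center. As the only between-establishment test specified, it can show that centers differ, but it cannot support the Discussion's aim to confirm better activation by type of establishment. That conclusion follows from the design and needs no numerical assumption.

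The size does need assumptions: with a between-center SD of 1 to 3 points, patient SD 15 and full enrollment, one test is significant 9% to 46% of the time with no navigator effect. The 14% to 16% familywise error is a smaller and separate matter, and correcting it would leave the main problem in place.

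This should be fixed. It affects how one analysis is described and read, not the study's implementation objectives.

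**What to change.** 1. **Statistical Analysis, Design.** Define the analysis as a descriptive comparison of mean 12-month change across the five centers. Report case-mix-adjusted differences from the navigator center with 95% confidence intervals. Add one sentence: only one center employs a navigator, so a difference between centers is not attributable to the navigator.
2. **Discussion.** Replace *confirm* with *explore* in the sentence on establishments that combine measures.
3. **Only if significance at 5% is kept for the four contrasts.** Use Dunnett-adjusted intervals (critical value about 2.4 to 2.5 in place of 1.96). No overall test is needed first, because the Dunnett procedure controls the familywise error by itself.

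The cost is wording and a weaker claim. No patients or data are added. With item 3, intervals become about 23% to 25% wider.

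### Four unadjusted centre comparisons of PAM-13 change, plus an unranked mixed model, are all judged at 5%, so a chance centre difference appears in roughly 13-18% of null trials

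*Protocol article*

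**What the plan says.** In the protocol article, the Design part of Statistical Analysis sets three measurement times: "Activation will be measured quantitatively at enrollment, at 6 months, and at 12 months". It then plans two comparisons of activation.

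- **Change score.** "The difference will be calculated between the baseline measurement and the 12-month measurement for all patients at each center". After that, "The mean of this difference will be compared between the comprehensive cancer center that employs a nurse navigator and each of the 4 other facilities". This makes four comparisons sharing one comparator centre.
- **Mixed model.** "Activation will also be compared according to its evolution during the 12 months of follow-up by using a mixed linear model". Its covariates are chosen from the data: "The variables influencing the difference in the activation score will be included in this model".

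Neither analysis is called main, supportive or descriptive, and the mixed-model term to be tested is not given. The section on the degree of significance has one rule: "The results will be considered significant at the 5% threshold". The missing-data section rules out imputation, so the change score can use only patients with both an enrolment and a 12-month score.

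Number of Subjects Needed says that a sample size for an efficacy hypothesis cannot be calculated. It caps enrolment at 600 in total, 150 per site, with two sites at no more than 75. The Discussion nevertheless describes "the objective being to confirm better activation of the patient in establishments that use a combined set of measures".

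**The concern.** PAM-13 is the central patient measure, and the Discussion gives the between-centre comparison a confirmatory purpose. Under the stated rules, any of the four change-score comparisons can be reported as significant at 5%, and so can whatever is tested in the mixed model.

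The analyses need not agree. The change score uses complete pairs only and has no stated adjustment. The mixed model can use the 6-month score and patients with incomplete follow-up, and it carries selected covariates. Without a ranking or an overall error limit, a reader of the results cannot tell whether a reported centre difference was the planned test or the most favourable of several. The planned recommendations for dissemination to other centres could then rest on a chance finding.

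**Working it through.** **Inputs from the protocol article.** Five centres; four comparisons against the navigator centre; visits at 0, 6 and 12 months; 5% per result; no imputation; site caps of 150 and 75.

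**Assumptions not in the article.** Two-sided tests (the article states this only for the factor search: "Student two-sided *t* test (or Wilcoxon test if the conditions are not met) for quantitative variables will be performed"); within-patient correlation 0.5, equal between all visits; covariance known in the mixed model; dropout at random; no covariate selection; navigator centre of either 150 or 75 patients.

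**Step 1: the plan's own figure.** 3 × 150 + 2 × 75 = 600, so the enrolment cap reproduces. The article states no power, effect size or overall error rate for activation.

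**Step 2: independent tests.** The chance of at least one false positive in k tests is 1 − 0.95^k. For k = 4 it is 1 − 0.8145 = 18.5%.

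**Step 3: shared comparator.** Two comparisons against the same centre of size n0 have correlation √[ni·nj / ((n0+ni)(n0+nj))].
- n0 = 150, ni = nj = 150: 150/300 = 0.50.
- n0 = 150, ni = nj = 75: 75/225 = 0.33.
- n0 = 75, ni = nj = 150: 150/225 = 0.67.

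Positive correlation pulls the rate below 18.5%, more so when the navigator centre is a small site. The t tests on change are scale-free, so this rate depends on relative centre sizes and not on the assumed 0.5.

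**Step 4: simulation with no centre difference** (6,000 trials per row; Monte Carlo standard error about √(0.16 × 0.84/6000) = 0.5 points). Dropout of 15% per interval leaves 0.85² = 72% with a 12-month score.

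| Navigator n | Dropout per interval | Any of 4 change comparisons | Global slope test (4 df) | Either of these | Any of 4, or any pairwise slope |
|---|---|---|---|---|---|
| 150 | 0 | 16.3% | 5.1% | 17.3% | 17.7% |
| 150 | 15% | 16.8% | 4.8% | 17.8% | 21.3% |
| 75 | 0 | 14.2% | 4.9% | 15.5% | 15.3% |
| 75 | 15% | 14.8% | 5.1% | 16.4% | 18.3% |

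Repeating the exercise with 0 to 50% missing at 12 months puts any-of-four at about 13-18%.

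**Step 5: what the second analysis adds** (from unrounded rates).
- As one global slope test: 17.33 − 16.25 = 1.1, 17.78 − 16.75 = 1.0, 15.48 − 14.17 = 1.3 and 16.38 − 14.80 = 1.6 points. An 8-df test with categorical time adds slightly more, 2.0-2.6 points (for example 18.80 − 16.25 = 2.6).
- If also read pairwise: 1.2-1.4 points with complete data and 3.5-4.5 with 15% dropout per interval, rising to about 5-7 under heavy dropout.

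**Step 6: like for like.** For one centre pair, with the change-score test set against the mixed-model contrast for that same pair, the verdicts differ in 0.6-0.7% of null trials with complete data, about 3% with 30% missing at 12 months and about 4-5% with 50% missing. The rate of either being positive is 5.1-5.3%, 6.7% and 8.0% respectively. With complete data at equally spaced visits and equal correlations, an unadjusted linear slope is simply the M12−M0 change rescaled, so near-agreement is expected.

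**The case against.** The strongest reply has four parts.

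- **No success rule exists.** The three stated objectives concern implementation, obstacles and facilitators, and recommendations; none is a between-centre test of activation. This stands against one tempting reading, that the study can win on whichever analysis reaches 5%. The article defines no success criterion and disclaims an efficacy hypothesis. It does not make the 5% verdicts harmless, because the Discussion states a confirmatory aim and the significance rule covers every result.
- **Having two analyses is not the main problem.** This also stands. A reader might infer that the two often contradict each other: comparing any-of-four with the 4-df global test gives disagreement in 11-15% of null trials. But that sets a procedure with an error rate near 15% against one near 5%. For the same pair of centres, disagreement is only 0.6-5%.
- **The wording may make the mixed model supplementary.** The text can be read as a simple comparison followed by an adjusted model, as it does for literacy, anxiety and quality of life. It does not say so, nor that the model retests the navigator contrast. Even on that reading, the four unadjusted comparisons remain.
- **The unseen analysis plan may settle the ranking.** It may, and the mere absence of model detail is not the point. The point is what the article fixes: four comparisons plus a further analysis of activation, under one blanket 5% threshold.

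**Conclusion.** The point holds in this form. Following the published rules, a significant centre difference in activation arises by chance in about 13-18% of trials from the four change-score comparisons alone, against a stated 5%. The unranked mixed model adds about 1-2 points as a global slope test and up to about 5-7 if also read pairwise under heavy dropout.

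The any-of-four range rests on the site caps and two-sided tests. The increments also rest on the assumed correlation of 0.5, known covariance and random dropout. Data-driven covariate selection is not simulated and could add more.

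The consequence is selective reporting of a centre difference against a confirmatory aim. It is worth correcting, but it does not threaten the implementation objectives.

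**What to change.** In the Design part of Statistical Analysis:

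1. Name the mixed model, using all available enrolment, 6-month and 12-month scores with time as a category, as the main activation analysis.
2. Take the four navigator-versus-other-centre differences in 12-month change from that model, each with a 95% CI. Either control significance claims at an overall two-sided 5%, or state that the comparisons are exploratory and carry no significance claim.
3. Keep the raw M12−M0 mean comparison as descriptive.

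For step 2, Holm starts at 0.05/4 = 0.0125 for the smallest p value. Dunnett uses the shared comparator and suits the authors' question directly. Gating by one global centre-by-time test is a further option: a single such test had a simulated error rate near 5%. It first asks whether any centres differ, however, which is not the navigator-versus-each question, and it protects fully only when no centres differ.

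The cost is wording: both analyses are already planned and no data collection or sample size changes. The downside is that single centre comparisons face a stricter threshold, or lose their significance claim if declared exploratory.
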